#### Multi-timepoint data analysis

2.9.2

For repeated-measures data satisfying the sphericity assumption, repeated-measures ANOVA will be applied. If the sphericity assumption is violated, Greenhouse-Geisser correction or multivariate ANOVA will be used. This analysis will examine the main effect of time on outcome measures and potential time-by-group interactions.

For non-normally distributed data or datasets with significant missing values across timepoints, mixed-effects models will be employed. These models accommodate unbalanced data and missing values while accounting for intra-individual correlations.

#### Missing data handling and dropout analysis

2.9.3

Missing Data: Multiple imputation will be used to address missing data, leveraging intervariable correlations to generate plausible values and enhance result accuracy.

Dropout Analysis: The primary analysis will follow the per-protocol approach, including only subjects who adhered strictly to the study protocol. As a supplementary strategy, intention-to-treat (ITT) analysis will include all randomized participants regardless of protocol deviations or dropout status, preserving randomization integrity and minimizing selection bias. Additionally, baseline characteristics (e.g., age, sex, initial depression scores) of dropouts versus completers will be compared using chi-square or t-tests to assess systematic bias. Significant differences will prompt covariate adjustment in regression models.

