#### Handling of dropouts

2.2.3

(1) Criteria for dropout

Patients who have provided informed consent, been screened and randomized for the trial, but for any reason do not complete the treatment and observation period as outlined in the study protocol will be considered dropouts.

(2) Handling of dropout cases

1) After a patient drops out, the researcher should contact the patient via home visits, scheduled follow-ups, phone calls, or letters to inquire about the reason for dropout, record recent sleep patterns, and complete any assessments that can be performed.

2) For patients who drop out due to allergies, adverse reactions, or treatment ineffectiveness, appropriate treatment measures should be taken according to their condition.

3) All dropout cases should be properly documented, both for archival purposes and for the required analysis in statistical evaluation. No additional patients will be recruited to replace dropouts.

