### Sample size

2.3

Based on the type of study, the sample size is calculated using PASS 15.0 software. The PSQI score of insomnia patients is chosen as the outcome measure. Based on literature and preliminary experimental results, the average PSQI score for the drug control group is 10.76 ± 3.32, and it is expected that the PSQI score in the insomnia group will decrease by 2.63 points. An effect size of 0.8 is used, with α = 0.05 and power = 0.9. The calculated sample size for each group (AA group, SAA group, control group) is N1 = N2 = N3 = 52. Considering a 20% dropout rate, the total sample size required is N1 = N2 = N3 = 65. According to previous reports [5], the prevalence of insomnia in adolescents is 20%, so the sample population is (N1 + N2 + N3) ÷ 20% = 975, then the sample population should be more than 975.

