### Randomization

2.5

After screening based on the inclusion and exclusion criteria, eligible adolescent insomnia patients will be randomly assigned in a 1:1:1 ratio to the AA group, SAA group, or control group. The randomization sequence will be generated by researchers who are not involved in the trial implementation or statistical analysis using SPSS 25.0 software. The sequence will be hidden using the envelope method, and each envelope will contain the randomization order for patient allocation. A designated person will be responsible for patient inclusion, and patients will receive the corresponding envelope in the order of enrollment.

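### One multiple imputation for all missing data can credit AA pupils who left for ineffectiveness or intolerance with the AA completers' benefit, moving the supplementary ITT result towards the per-protocol result

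*Protocol article*

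**What the plan says.** Section 2.9.3 (Missing data handling and dropout analysis) gives a single rule for missing values: "Multiple imputation will be used to address missing data, leveraging intervariable correlations to generate plausible values and enhance result accuracy". It does not distinguish reasons for missingness, and it does not say whether the imputation model includes treatment arm or interim scores. The same section makes per-protocol the primary analysis and ITT, covering everyone randomised, a supplement. Its only check on dropout is a comparison of baseline characteristics between dropouts and completers, followed by covariate adjustment if they differ.

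Section 2.2.3 (Handling of dropouts) names reasons tied to the result or tolerability of treatment: "For patients who drop out due to allergies, adverse reactions, or treatment ineffectiveness, appropriate treatment measures should be taken according to their condition". It also tells researchers to contact pupils who leave, ask why, and carry out whatever assessments are still feasible.

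Section 2.3 (Sample size) sets the scale: "Considering a 20% dropout rate, the total sample size required is N1 = N2 = N3 = 65".

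**The concern.** Standard multiple imputation is valid when, given the observed data, pupils with missing scores resemble pupils whose scores were seen. A pupil who leaves because treatment did not help or was not tolerated is a likely exception. If the imputation is done by arm, or with arm in the model, and that pupil has no score after leaving, the missing PSQI and BDI values are drawn from what AA completers with a similar baseline achieved.

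The per-protocol analysis removes such pupils. ITT is the stated analysis that keeps them, so it is the one that could show what their removal does. If ITT fills them in from completers of the same arm, it drifts back towards the per-protocol answer, and agreement between the two is partly built in. The baseline comparison does not help: a pupil with an ordinary baseline who left because treatment failed looks like everyone else on it.

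**Working it through.** **Inputs**

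- 65 randomised per arm, 20% dropout (section 2.3), allocation 1:1:1 (section 2.5).
- SD 3.32: "the average PSQI score for the drug control group is 10.76 ± 3.32".
- Difference 2.63 points: "it is expected that the PSQI score in the insomnia group will decrease by 2.63 points".
- Share of dropouts by reason: not given, so varied below.

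**Assumption on the effect.** Section 2.3 does not call 2.63 a between-arm difference, and it attaches the SD to a drug control group that this trial does not have. Reading them as the AA-versus-comparator difference and its SD is therefore an assumption. It fits the stated effect size: 2.63 / 3.32 = 0.79, against "An effect size of 0.8 is used".

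**The plan's own figures.** The dropout inflation reproduces: 52 / (1 − 0.20) = 65 per arm, so dropout is 0.20 × 65 = 13 per arm. The 52 itself does not follow from the stated effect size, alpha and power (a two-sided two-group comparison needs 33 to 35 per group). That is a separate matter and does not enter below.

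**Size of the overstatement.** Suppose affected AA dropouts truly end at the comparator's mean but are imputed at the AA completers' mean.

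- Overstatement = (share of the AA arm affected) × 2.63.
- SE = 3.32 × √(2/n): 3.32 × √(2/65) = 0.582; 3.32 × √(2/52) = 0.651.

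The last column comes from a simulation with 65 per arm, 20% missing in both arms, regression imputation on baseline within arm, 20 imputations, an assumed baseline correlation of 0.5 and 600 runs. It divides by the standard error that the imputation itself produces (about 0.64).

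| AA dropouts affected | Points | In SE, n = 65 | In SE, n = 52 | In SE, simulated |
|---|---|---|---|---|
| A quarter | 0.05 × 2.63 = 0.13 | 0.23 | 0.20 | 0.21 |
| Half | 0.10 × 2.63 = 0.26 | 0.45 | 0.40 | 0.36 |
| All | 0.20 × 2.63 = 0.53 | 0.90 | 0.81 | 0.80 |

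The simulated value for half is a little low partly because half of 13 was rounded to 6. With dropout in the AA arm only and all of it affected, the simulation gives 0.87 SE.

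**Effect on the conclusion.** With all affected, the ITT effect is truly 2.63 − 0.53 = 2.10 points but is reported as about 2.63, which is 1 / 0.80 = 1.25 times the true value. The true effect still stands at 2.10 / 0.582 = 3.6 SE by the simple formula, or 2.10 / 0.645 = 3.3 SE with the simulated standard error. Both lie far beyond 1.96.

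**The case against.** The strongest reply is that reason-specific imputation and sensitivity analyses belong in an analysis plan, and only a condensed protocol article is shown. That stands against any complaint that detail is absent. It does not dispose of the point, because section 2.9.3 states a rule for all missing data and section 2.2.3 of the same document names dropout reasons under which that rule can fail.

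Other objections stand and limit the claim:

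- **Data after dropout.** Section 2.2.3 asks for feasible assessments after a pupil leaves, so some of these pupils will have observed scores. A dropout there is anyone who does not complete treatment and observation, so 20% dropout need not mean 20% missing outcomes. Collection is best-effort, however, and section 2.9.3 does not say how such scores enter ITT.
- **Imputation model.** It is not stated. A model without arm would pull values towards the pooled mean and bias the result differently. Crediting AA is possible, not certain.
- **Direction.** Pupils in the SAA and control arms may also leave because nothing helped. Imputing them from their own completers would flatter the comparator and offset the bias.
- **Mixed models.** Section 2.9.2 offers them when many values are missing, but they too rely on observed data explaining the missingness, so they are not an independent check.

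A reader might infer that the plan will inflate the AA effect by nearly one standard error. The documents do not support that. The 0.90 figure needs every AA dropout to be of this kind, to lose the whole benefit and to have no later score, with no offset elsewhere. Nor is it a ceiling: affected dropout of 25% would give 0.25 × 2.63 / 0.582 = 1.13 SE. A reader might also infer that a false positive is in prospect; at the planned effect, significance does not change.

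**Conclusion.** The point holds in a limited form. A single correlation-based imputation for all missing data sits poorly with dropout reasons that the protocol itself ties to treatment outcome and tolerability, and the planned baseline check cannot detect the resulting bias. If arm is in the imputation model and later scores are lacking, the plausible overstatement of the ITT effect runs from about 0.2 SE to 0.8–0.9 SE, according to the share of AA dropouts affected. This rests on 2.63 points as the between-arm difference, SD 3.32, 20% dropout in the AA arm, affected pupils ending at the comparator's mean, and no offset in the comparator.

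What is at stake is the size of a supplementary estimate and its value as a check on the primary one. The choice of per-protocol as primary analysis, which excludes these pupils altogether, is a separate and weightier issue. Making ITT primary would not by itself cure the present one, since ITT would carry the same imputation.

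**What to change.** In section 2.9.3:

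1. State that scores collected after dropout under section 2.2.3 enter ITT as observed.
2. Keep standard multiple imputation for what remains missing.
3. Add one pre-specified sensitivity analysis in which still-missing PSQI and BDI scores of AA and SAA pupils who left for ineffectiveness, allergy or adverse reaction are imputed from the control arm's distribution given baseline.
4. Report both ITT results, and call the AA conclusion robust only if it holds under both.

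Other departures from the standard assumption, such as delta adjustment or a tipping-point analysis, could serve the same purpose. Control-based imputation is suggested because it needs no additional parameter and uses reasons that section 2.2.3 already asks researchers to obtain.

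The cost is one extra imputation run and a few lines of text, with no new data and no change to trial conduct. The second estimate may be less favourable to AA. The change leaves the per-protocol primary analysis untouched.

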## Discussion

3

This study is a single-center, double-blind, randomized controlled trial aimed at evaluating the efficacy of AA in improving sleep and observing its impact on the occurrence of depression following insomnia in adolescents. The goal is to provide new insights into the prevention of adolescent depression.

Insomnia is closely related to depression (34). Adolescence is a critical period for the development of personality and traits, during which adolescents also experience a “perfect storm” of sleep changes. Many factors contribute to the increased susceptibility to insomnia during this period. The reduced sleep drive in adolescence, the extended intrinsic circadian cycle of the endogenous clock, and the delayed secretion of melatonin interact with external factors such as participation in extracurricular activities, heavy homework, use of electronic devices at night, and early school start times, leading to delayed sleep onset and reduced sleep duration. Over time, these factors result in the occurrence of insomnia (35, 36). In China, the education system differs from that of other countries, with heavy homework loads and dense curricula, making academic pressure an inevitable source of stress for Chinese adolescents (37), which is one of the key factors contributing to insomnia (38).

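### The per-protocol set is the primary analysis and intention-to-treat only supplementary, so the main efficacy result rests on a group selected after randomisation

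*Protocol article*

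**What the plan says.** Section 2.9.3 fixes the order of the two analysis sets. On the main one: "The primary analysis will follow the per-protocol approach, including only subjects who adhered strictly to the study protocol". On the other: "As a supplementary strategy, intention-to-treat (ITT) analysis will include all randomized participants regardless of protocol deviations or dropout status", which the same sentence credits with "regardless of protocol deviations or dropout status, preserving randomization integrity and minimizing selection bias". No other section names a different primary population.

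Other parts of the article bear on who would be left in the per-protocol set:

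- Section 2.2.3 counts as a dropout any randomised patient who "for any reason do not complete the treatment and observation period as outlined in the study protocol will be considered dropouts". It provides for care "For patients who drop out due to allergies, adverse reactions, or treatment ineffectiveness", and it rules out replacement.
- Section 2.2.4 allows stopping when a patient's condition worsens. Section 2.10 provides for termination when severe depression is found. I read both as acting on the individual participant.
- Section 2.9.3 also says "Multiple imputation will be used to address missing data", and it plans a baseline comparison of dropouts with completers, with covariate adjustment if they differ.
- The Discussion describes the trial as "aimed at evaluating the efficacy of AA in improving sleep and observing its impact on the occurrence of depression following insomnia in adolescents".

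**The concern.** The word superiority is not used. However, an efficacy question against sham and education, with no equivalence or non-inferiority margin, is a superiority question. For such a question the set that supports a causal reading is everyone randomised, analysed as assigned. A strict-adherer set is defined by what happens after randomisation, and here the article itself ties leaving to poor response.

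The link is direct for the co-primary BDI. Depression incidence is derived from BDI thresholds (section 2.9), and a participant taken out for severe depression would not be a strict adherer. The primary set can therefore lose the events that the prevention question has to count.

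Strict adherence also asks different things of different arms. AA participants press beans 3–5 times a day and change ears every 3 days; SAA participants press tape under the same instructions; control participants receive education only. Skin reactions to beans or tape cannot occur in the control arm.

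At stake is the headline PSQI and BDI comparison. It could show an effect that does not exist, or hide one that does, and a reader could not tell which from the primary result alone.

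**Working it through.** **Inputs from the article.** Section 2.3 gives SD 3.32, planned difference 2.63 points, 52 evaluable and 65 randomised per group, and 20% dropout. The SD comes from a drug control group, which is not an arm of this trial; I use it because it is the only one given. The two-sided 5% level is assumed, since the article gives α = 0.05 without sidedness.

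**The plan's own figure.** The dropout step reproduces: 52 / (1 − 0.20) = 65 per group. The planned loss is 65 × 0.20 = 13 per group, or 39 of 195.

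**Assumptions not in the documents.** There is no true difference between AA and one comparator. Both arms lose the same fraction f. In each arm, leaving depends on a score that correlates ρ with a poor PSQI outcome (ρ = 0 means random loss).

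**Formula.** If an arm loses the top fraction f on that score, its remaining mean falls by ρ × SD × φ(z) / (1 − f), where z is the (1 − f) quantile of the standard normal. The bias in the contrast is the difference between the two arms' shifts.

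- f = 0.20: z = 0.842, φ(z) = 0.280; 0.280 / 0.80 × 3.32 = 1.16 points at ρ = 1. That is 1.16 / 2.63 = 44% of the planned difference.
- f = 0.10: z = 1.282, φ(z) = 0.1755; 0.1755 / 0.90 × 3.32 = 0.65 points at ρ = 1.
- Other correlations at f = 0.20: 0.5 × 1.16 = 0.58; 0.3 × 1.16 = 0.35; ρ = 0.5 against 0.3 gives 0.2 × 1.16 = 0.23.

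**Simulated type I error** (two-sample t-test, 65 randomised per arm, no true effect, f = 0.20). A positive bias favours AA.

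| ρ in AA | ρ in comparator | Bias (points) | Type I error |
|---|---|---|---|
| 0 | 0 | 0 | 5% |
| 0.5 | 0.5 | 0 | about 6% |
| 0.5 | 0.3 | 0.23 | about 7% |
| 0.3 | 0.5 | −0.23 | about 7% |
| 0.3 | 0 | 0.35 | 8–9% |
| 0.5 | 0 | 0.58 | about 15% |
| 0.7 | 0 | 0.81 | 26–27% |
| 1.0 | 0 | 1.16 | about 49% |

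With f = 0.10 and random loss in the comparator, type I error is about 6%, 8%, 11–12% and 19% at ρ = 0.3, 0.5, 0.7 and 1.0. Analysing all randomised patients with their outcomes observed stays near 5% throughout.

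**Power if intention-to-treat becomes primary.** The standardised effect is 2.63 / 3.32 = 0.792. With 65 per arm, two-sided 5%, exact t-test:

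- full effect in everyone: 99.4%;
- the 20% who drop out gain half the effect (0.792 × 0.9 = 0.713): 98.1%;
- the 20% who drop out gain nothing (0.792 × 0.8 = 0.634): 94.8%, or 88.1% at a Bonferroni level of 0.05/3.

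**Can the listed safeguards repair the primary analysis?** Multiple imputation fills in missing outcomes, but non-completers are already outside a strict-adherer set, so little is left to impute there. The same holds for the mixed models in section 2.9.2. The dropout-versus-completer comparison, and the adjustment it triggers, covers measured baseline factors. It cannot correct selection on response to treatment.

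**The case against.** The strongest reply is that bias is a risk here, not a demonstrated fact. Section 2.2.3 gives no rate of dropout for ineffectiveness; it only says what care follows. The largest figures need loss that depends wholly on outcome in AA and is random in the other arm, and nothing in the article supports that asymmetry. Between AA and SAA the case for unequal loss is weaker still: the tape looks identical, the pressing instructions are the same, and participants and evaluators are blinded. Equal outcome-related loss nearly cancels, and if failures leave the comparator instead, the bias goes against AA. Moreover, an intention-to-treat analysis is already planned, dropouts are to be contacted and assessed where feasible, and a disagreement between the two analyses would be visible. Imputation may simply be meant for the intention-to-treat analysis, in which case there is no contradiction.

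Most of this stands as a limit on size and wording. The 49% is an upper extreme, the range includes zero and reversed bias, and the difference in adherence burden applies mainly to comparisons with the education-only control. The imputation plan is not a separate defect; it only fails to rescue the primary set. None of this gives a reason for making per-protocol primary. A supplementary analysis can expose a discrepancy, but it does not decide the trial.

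**Conclusion.** The concern holds. The article states a rule, rather than leaving a detail open, and the rule places a post-randomisation subset above the full randomised comparison in what is in substance a superiority trial. The article also credits the lower-ranked analysis with the very property that the primary one lacks.

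Under the assumptions set out above, the possible PSQI bias at 20% loss runs from none, through about 0.2 points either way for modestly unequal loss and about 0.6 points (type I error about 15%) for clearly unequal loss, to a ceiling of 1.16 points (about 49%). Which of these would apply cannot be known beforehand, and the per-protocol data cannot reveal it afterwards. That is enough to require the change before any analysis.

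**What to change.** In section 2.9.3, and in the SAP if one exists, exchange the two roles:

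- **Primary:** all randomised participants in the arm assigned, using all observed PSQI and BDI data, by a likelihood-based mixed model or by multiple imputation followed by ANCOVA. The article already names mixed models and multiple imputation.
- **Sensitivity:** per-protocol, labelled as such, with the adherence criteria fixed before unblinding.
- **Data collection:** keep obtaining PSQI and BDI after a participant stops treatment. Section 2.2.3 already foresees contacting dropouts and completing what assessments are possible.

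The cost is one paragraph. No extra participants are needed, since 65 per group are to be randomised already. The estimated effect may be somewhat smaller than in strict adherers.

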### Statistical analysis

2.9

Statistical analyses will be performed using SPSS 25.0 (SPSS, Chicago, IL, USA). The incidence of adolescent depression will be calculated based on the Beck Depression Inventory (BDI) thresholds established in prior studies. Continuous variables will be presented as mean ± standard deviation, while categorical data will be expressed as percentages or proportions. A p-value <0.05 will be considered statistically significant for intergroup differences, and p<0.01 will indicate highly significant differences.

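### The dropout check names no arm, so it can miss attrition that unbalances the arms in the per-protocol analysis, and it alone triggers adjustment for attrition.

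*Protocol article*

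**What the plan says.** Section 2.9.3 (Missing data handling and dropout analysis) sets the check and its purpose: "baseline characteristics (e.g., age, sex, initial depression scores) of dropouts versus completers will be compared using chi-square or t-tests to assess systematic bias". It then attaches a decision: "Significant differences will prompt covariate adjustment in regression models". No arm, within-arm comparison or arm-by-dropout term is named.

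The same section makes the per-protocol set primary: "The primary analysis will follow the per-protocol approach, including only subjects who adhered strictly to the study protocol". Intention-to-treat is supplementary: "intention-to-treat (ITT) analysis will include all randomized participants regardless of protocol deviations or dropout status". It also states "Multiple imputation will be used to address missing data", without naming the imputation variables.

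The 0.05 level is given in section 2.9 for comparisons between groups: "A p-value <0.05 will be considered statistically significant for intergroup differences". I take it to apply to the dropout check too. Section 2.9.1 compares the groups by one-way ANOVA and names no baseline covariate.

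**The concern.** The trial estimates AA against sham (SAA) and against control. When dropouts are removed from the primary analysis, that contrast is distorted if the people left in one arm differ from those left in another. A test of all dropouts against all completers asks a different question: whether leavers differ from stayers overall. If sicker pupils leave one arm and healthier pupils leave another, the two patterns cancel in the pooled comparison but add up in the contrast between the arms.

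The test also has a consequence, because adjustment for attrition follows only if it is significant. Where selection differs by arm, adjustment for baseline would help, but the trigger may not fire.

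Reasons for leaving that differ by arm are plausible here. Section 2.2.3 foresees them: "For patients who drop out due to allergies, adverse reactions, or treatment ineffectiveness". Only the AA and SAA arms wear tape, while control receives education alone. The word pooled is my reading, not the document's: a t-test of dropouts against completers has two groups, and no arm is mentioned.

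**Working it through.** **Inputs from section 2.3.** 52 evaluable per arm, 20% dropout, 65 randomised per arm, design effect 0.8 SD, PSQI SD 3.32. The inflation step reproduces: 52 / (1 − 0.20) = 65. That gives 65 − 52 = 13 dropouts per arm, or 39 in all.

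**Assumptions not in the documents.** Standard normal baseline score. Dropouts are drawn within each arm with probability weight exp(s·x), where x is the baseline score in SD units and s is the selection strength. Positive s means sicker pupils leave. Baseline-outcome correlation is 0.6.

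**Method.** At least 4,000 simulated trials per scenario. The pooled test is a two-sample t-test at 0.05. The by-arm test compares the dropout-completer difference in AA with that in control. The gap is the absolute AA-control baseline difference among completers.

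| s in AA / SAA / control | Dropouts per arm | Pooled test fires | By-arm test fires | Completer gap |
|---|---|---|---|---|
| +0.8 / +0.8 / +0.8 | 13 / 13 / 13 | over 99% | about 5% | 0.00 SD |
| +0.8 / 0 / −0.8 | 13 / 13 / 13 | 3-5% | about 97% | about 0.32 SD |
| +0.5 / 0 / −0.5 | 13 / 13 / 13 | 4.7% | about 70% | 0.21-0.22 SD |
| +0.8 / 0 / 0 | 13 / 13 / 13 | about 32% | 48% | 0.16-0.17 SD |
| +0.8 / +0.8 / 0 | 13 / 13 / 13 | about 88% | 48% | as row above (AA and control unchanged) |
| +0.8 / +0.8 / +0.8 | 20 / 13 / 7 | over 99% | 6-7% | 0.17 SD |

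**From baseline gap to outcome bias.** For a comparison of post-treatment scores, unadjusted bias = correlation × gap.

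- Opposite directions: 0.6 × 0.32 = 0.19 SD, or 0.19 × 3.32 = about 0.6 PSQI points. Against the design effect, 0.19 / 0.8 = 24%.
- Sicker leave AA only: 0.6 × 0.16 = about 0.10 SD.
- Same direction at 20 / 13 / 7: 0.6 × 0.17 = about 0.10 SD.

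In all three cases AA's completers start less ill than control's, so the bias flatters AA.

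**A second dropout model.** With logistic dropout at an expected 20% per arm and the same correlation:

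- Same slope of 0.8 in all arms: pooled test fires in 98.7%, bias 0.00 SD.
- Slopes +0.8 / 0 / −0.8: pooled test fires in 5.0%, bias 0.18 SD. Adjusting for baseline brings the bias to about zero.
- Same slope, dropout 30 / 20 / 10%: bias 0.08 SD. The pooled test fires in 98% and the arm-by-dropout interaction in 5%.
- Same slope, equal rates, AA effect varying by −0.3 per SD of baseline: bias 0.05 SD, and baseline adjustment does not remove it.

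**The case against.** **The opposite-direction pattern is an assumed worst case.** It needs mirror-image selection on baseline severity at equal rates. The dropout reasons in section 2.2.3 appear in an instruction on care after dropout and predict no such pattern. Tape allergy has no stated link to baseline PSQI or BDI, and AA and SAA use the same tape. This stands, and it limits how likely the 3-5% case is. The milder case, where sicker pupils leave AA only, needs no cancellation and is still missed in about two trials in three.

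**A reader might infer that the pooled test is worthless, or that it only raises false alarms.** The documents and the figures do not support that. Same-direction selection is harmless only if dropout rates are similar across arms and AA's effect does not vary with baseline. At 20 / 13 / 7 dropouts the pooled test flags a real gap in over 99% of trials, while the arm-by-dropout test fires in 6-7%. A false alarm also does little harm, since it only prompts adjustment.

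**A reader might set the 0.32 SD gap against the 0.8 SD design effect and read a bias of 40%.** That divides a baseline difference by an outcome effect. The outcome bias is about 24% at a correlation of 0.6. In a change-from-baseline or time-by-group comparison, which section 2.9.2 also plans, the same gap gives 0.32 × (1 − 0.6) = about 0.13 SD against AA.

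**Other safeguards exist.** Multiple imputation, mixed models and the supplementary intention-to-treat analysis may reduce the bias. This is fair, but the primary analysis remains per-protocol.

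**Dropout tables by arm are commonly left to a fuller document.** Agreed, and their absence is not the point. The protocol does not treat a non-significant result as proof of no bias either. The point is that it states a test and a decision rule, and the rule has no arm term.

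**Conclusion.** The concern holds in limited form. The stated check does not measure whether those who remain differ between arms, yet that is what biases the AA contrast in the primary analysis. It can therefore leave adjustment untriggered when it is needed: it fires in 3-5% of trials under opposite-direction dropout (baseline gap about 0.32 SD, outcome bias about 0.19 SD) and in about 32% when sicker pupils leave AA only (gap about 0.16-0.17 SD, outcome bias about 0.10 SD).

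These sizes rest on assumed selection strengths, 13 dropouts of 65 per arm except in the unequal-rate row, a baseline-outcome correlation of 0.6 and the two-group reading of the text. They show what the rule can miss, not what will happen in this trial. The arm-by-dropout test is no full replacement, because it misses bias from unequal rates with similar selection. The point deserves a change because the rule governs adjustment of a per-protocol primary analysis and the remedy uses data already collected.

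**What to change.** Replace the single comparison in section 2.9.3 with an assessment by arm that uses three items together:

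1. Dropout rate and reason in each arm.
2. Baseline PSQI and BDI of dropouts and completers within each arm, with the arm-by-dropout term.
3. The between-arm difference in baseline PSQI and BDI among those analysed, with a 95% confidence interval.

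Base the judgement mainly on items 1 and 3. Item 2 misses same-direction selection at unequal rates and has limited power in milder cases. Decide in advance whether the analysis is adjusted for baseline PSQI and BDI, and do not let the pooled p-value decide it.

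The cost is one sentence of analysis wording and one more table. No new data are needed.

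### A significance test of dropouts against completers decides whether regression models are covariate-adjusted, and no adjustment of the treatment comparison is fixed regardless of that test

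*Protocol article*

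**What the plan says.** Under Missing data handling and dropout analysis (2.9.3), baseline characteristics, with age, sex and initial depression scores given as examples, "of dropouts versus completers will be compared using chi-square or t-tests to assess systematic bias". The next sentence is the rule at issue: "Significant differences will prompt covariate adjustment in regression models". The regression models are not identified and the list of characteristics is not closed.

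No threshold is attached to this test. The nearest is the general one in section 2.9: "A p-value <0.05 will be considered statistically significant for intergroup differences".

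The treatment comparisons are one-way ANOVA or rank-sum tests (2.9.1) and repeated-measures ANOVA or mixed-effects models (2.9.2). None names a covariate. Section 2.9.4 has its own p<0.05 screen, but that selects factors associated with depression for a logistic model and is not a rule for adjusting the treatment effect.

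Section 2.9.3 also makes the per-protocol analysis primary, with ITT as a supplement, and plans multiple imputation.

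**The concern.** Whether a treatment-effect regression is adjusted, and for what, should be settled before the data are seen. Here it follows from a test run on trial data, and the test answers the wrong question in two ways.

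First, a non-significant result with few dropouts does not show that they resemble completers, and a significant one does not show that the variable predicts outcome. Predicting outcome is what makes adjustment useful.

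Second, the comparison sets all dropouts against all completers. The treatment contrast is biased mainly when the relation between dropout and a prognostic variable differs between arms, and pooling can hide exactly that.

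At stake is a model that can come out adjusted or unadjusted by chance, and a bias check that often stays silent when it is needed. This matters more than usual because dropouts leave the primary, per-protocol comparison.

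**Working it through.** **The plan's own numbers.** Section 2.3 gives 52 evaluable per group and says "Considering a 20% dropout rate".
- Inflation: 52 / (1 − 0.20) = 65 per group, as stated.
- Total: 3 × 65 = 195; screening 195 / 0.20 = 975, as stated.
- Expected dropouts: 0.20 × 195 = 39; completers: 195 − 39 = 156. Within one arm: 13 and 52.

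The article states no power for the dropout test, so there is no figure to reproduce there.

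**Power of the dropout test.** Two-sample t-test, two-sided alpha 0.05 (assumed from section 2.9). For a true baseline difference of d SD, the noncentrality is d × √(n₁n₂ / (n₁ + n₂)).
- Pooled: √(39 × 156 / 195) = √31.2 = 5.59, on 193 df.
- One arm: √(13 × 52 / 65) = √10.4 = 3.22, on 63 df.
- About 10% dropout, pooled: √(20 × 175 / 195) = √17.9 = 4.24, on 193 df.

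| d (SD) | 39 v 156 | 20 v 175 | 13 v 52 |
|---|---|---|---|
| 0.2 | 20% | – | 10% |
| 0.3 | 39% | 24% | 16% |
| 0.4 | 60% | – | 25% |
| 0.5 | 79% | 56% | 36% |
| 0.6 | 92% | – | 48% |

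Power of 80% needs about 0.505 SD pooled and about 0.885 SD within one arm. For sex, a split of 50% against 65% is detected 39% of the time at 39 v 156.

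**Chance triggers.** With no true difference and three independent tests, 1 − 0.95³ = 0.143, or 14%. Three is the number of examples in 2.9.3.

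**What the rule does to the treatment contrast.** This is an illustrative simulation with no true treatment effect. It assumes one baseline covariate correlated 0.5 with outcome, about 20% dropout, and AA against one comparator among completers.
- *Dropout unrelated to the covariate.* The SE of the treatment difference is 0.174 SD if always adjusted, 0.199 under the rule and 0.200 if never adjusted. Type I error stays near 5% throughout.
- *Dropout related to the covariate in the same way in all arms.* The test triggers 39% of the time; there is no bias of note and type I error stays near 5%.
- *Dropout related in opposite directions between AA and its comparator (log-odds slope 0.5 per SD).* The pooled test triggers only 15% of the time. Bias is −0.083 SD under the rule, 0.000 if always adjusted and −0.097 if never adjusted. Type I error is 7.2%, 4.9% and 7.5%.

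**Precision from fixed baseline adjustment.** Residual variance falls by the square of the baseline–outcome correlation r: 0.4² = 16% to 0.6² = 36%. The article gives no r, so 0.4 to 0.6 is an assumption.

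**The case against.** The strongest reply is that the sentence is a secondary attrition check. It comes after the supplementary ITT analysis and refers to unnamed regression models, while the main comparisons are ANOVA-type. Multiple imputation, mixed models and ITT also address missing data, and none depends on this test. A statistical analysis plan that is not shown may fix a covariate set.

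Much of that stands, and it limits the point:
- A reader might infer that the final or primary model hinges on the pre-test. The article does not say so; it says regression models, and its named comparisons carry no covariates.
- A reader might call the test underpowered without qualification. In the pooled comparison at 20% dropout it has about 80% power at 0.5 SD and more beyond that. Power is low for smaller differences, within single arms, or with fewer dropouts.
- A reader might conclude that the rule inflates type I error. In the simulation it did not when dropout was unrelated to the covariate or related alike in all arms. With arm-dependent dropout the error rate was close to that of never adjusting; the rule's failing is that it hardly corrects the bias.
- A reader might blame the trigger for lost precision. That loss comes mainly from the absence of a baseline covariate in the ANOVA; deleting the trigger alone recovers none of it.

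What does not stand is the suggestion that this is only missing detail. The data-dependent rule is written into the article, and a fixed covariate list elsewhere would leave it in conflict with that list unless it is removed.

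**Conclusion.** The point holds as a stated rule that is badly chosen, and it should be changed before analysis. It does not invalidate the trial. Baseline differences of 0.2 to 0.4 SD between dropouts and completers would go undetected about 80%, 61% and 40% of the time, while three independent tests with nothing to find would still switch adjustment on 14% of the time. The pooled contrast is also the wrong one for bias in the treatment effect.

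These figures assume exactly 20% dropout, a two-sided 0.05 threshold carried over from section 2.9, and, for the 14%, independence of three tests. The simulated bias rests on an assumed correlation of 0.5 and a deliberately unfavourable dropout pattern, so it shows the mechanism and does not forecast this trial. That no other adjustment applies is read from this article alone.

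**What to change.** In section 2.9.3, delete the sentence that makes adjustment depend on significant differences. Replace it with a statement that the PSQI and BDI treatment-effect models (ANCOVA or mixed model) adjust for the baseline value of the outcome, age and sex whatever the dropout comparison shows, and that the same variables enter the multiple imputation already planned.

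Keep the dropout-versus-completer comparison as description, shown by arm. Testing within arms would not be a substitute for fixed adjustment: at 13 v 52 the power is 16% for 0.3 SD.

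Cost: the one-way ANOVA in 2.9.1 becomes an ANCOVA, which means a matching edit there and a little more analysis work. The variables are already collected and the sample size stays at 65 per group. Any precision gain depends on the baseline–outcome correlation and comes from adding the baseline covariate.
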